# Comparing cognitive behavioural therapy for eating disorders integrated with behavioural weight loss therapy to cognitive behavioural therapy-enhanced alone in overweight or obese people with bulimia nervosa or binge eating disorder: study protocol for a randomised controlled trial

**DOI:** 10.1186/s13063-015-1079-1

**Published:** 2015-12-18

**Keywords:** Obesity, Binge eating, Psychotherapy, Weight management

## Abstract

**Background:**

Around 40 % of individuals with eating disorders of recurrent binge eating, namely bulimia nervosa and binge eating disorder, are obese. In contrast to binge eating disorder, currently there is no evidence base for weight management or weight loss psychological therapies in the treatment of bulimia nervosa despite their efficacy in binge eating disorder. Thus, a manualised therapy called HAPIFED (Healthy APproach to weIght management and Food in Eating Disorders) has been developed. HAPIFED integrates the leading evidence-based psychological therapies, cognitive behavioural therapy-enhanced (CBT-E) and behavioural weight loss treatment (BWLT) for binge eating disorder and obesity respectively. The aim of the present study is to detail the protocol for a randomised controlled trial (RCT) of HAPIFED versus CBT-E for people with bulimia nervosa and binge eating disorder who are overweight/obese.

**Method/Design:**

A single-blind superiority RCT is proposed. One hundred Brazilian participants aged ≥ 18 years, with a diagnosis of bulimia nervosa or binge eating disorder, BMI > 27 to < 40 kg/m^2^, will be recruited from both community and clinics and individually randomised to a therapy arm. Five groups of ten participants will receive the experimental intervention (HAPIFED) and the other five groups of ten the control intervention (CBT-E). Both therapies are manualised, and in this RCT will comprise 1 individual session and 29 office-based group sessions over 6 months. Assessment points will be at baseline, end of therapy, and 6 and 12 months after end of therapy. The primary outcome of this intervention will be reduced weight. Secondary outcomes will be improved metabolic indicators of weight management, reduction in eating disorder symptoms including improved control over eating, improved adaptive function, physical and mental health-related quality of life, and reduced levels of depression and anxiety.

**Discussion:**

This study will be the first to investigate a psychological therapy that aims to assist weight management in people with co-morbid overweight or obesity bulimia nervosa as well as with binge eating disorder. It will have the potential to improve health outcomes for the rapidly increasing number of adults with co-morbid obesity and binge eating disorder or bulimia nervosa.

**Trial registration:**

US National Institutes of Health clinical trial registration number NCT02464345, date of registration 1 June 2015.

**Electronic supplementary material:**

The online version of this article (doi:10.1186/s13063-015-1079-1) contains supplementary material, which is available to authorized users.

## Background

The combined general population lifetime prevalence of bulimia nervosa (BN) and binge eating disorder (BED) is around 5 % in women and 3 % in men [1]. Both disorders are characterised by recurrent binge eating or uncontrolled overeating episodes which, in the case of BN are also associated with regular compensatory weight control behaviours (e.g., self-induced vomiting) [2, 3]. It is now recognised that an increasing number, now around 40 % of people in the community with BN or with BED are obese [4, 5]. In clinics the prevalence is even higher, up to 80 % [6, 7]. Bulik et al. suggested, in a paper to highlight the issues of managing weight and eating disorders, that ‘BN in the overweight and obese patients may represent the natural evolution of the eating disorder on the backdrop of the obesity epidemic’ (Bulik et al., p.6) [8]. They wrote about the increase in clinical presentations of overweight and obese patients with BN and their requests for help with weight management. They argued that due to the rise in combined prevalence of co-morbid obesity and BN and BED, and their shared risk and maintaining features, an urgent need for new approaches to management is needed [8].

Patients with co-morbid BN or BED and obesity are currently faced with a problematic choice. Community-based studies [9, 10] indicate that while individuals with BN and BED frequently seek help in order to lose weight, most evidence-based psychological treatments such as cognitive behavioural therapy (CBT) for eating disorders fail to aid weight loss [11, 12]. In one study, Brody et al. [13] found the majority (63 %) of people with BED and co-morbid obesity chose CBT over a behavioural weight loss treatment (BWLT). However, 50 % of those who chose BWLT also thought their primary problem was BED and not obesity. Individuals with BN or BED and obesity may consequently undergo years of treatment for weight loss without attention to binge eating and its associated psychological co-morbidities [14, 15]. Further, whilst approaches such as BWLT for obesity are associated with weight loss in BED, weight regain is common [8] and whereas dietary restriction in normal weight people, with BN risks exacerbating the cycle of bingeing and fasting, as suggested by the classic Keys study of starvation [16], this may well differ for dietary restriction that is part of a supervised BWLT programme in people who are obese. As Bulik discussed, there may actually be harm from not addressing unchecked obesity [8]. A recent systematic review suggests that even very high levels of dietary restriction, as in low or very low energy diets, do not exacerbate binge eating, at least in BED [17]. Individuals with binge eating and obesity seek help to lose weight, but further research to establish the safety of weight loss treatment in BN is needed. In sum, BWLT fail to address the eating disorder and conversely psychological treatments fail to aid weight loss.

To address the need for treatment of BN and BED co-morbid with obesity, a manualised therapy called a Healthy APproach to weIght management and Food in Eating Disorders (HAPIFED) was developed ([name] et al., manuscript in preparation). This therapy aims to integrate features of the leading evidence-based psychological therapies for BN and BED, CBT-enhanced (CBT-E) [18, 19] with a specific BWLT for weight loss and reduced binge eating in BED [20, 21]. In HAPIFED, like BWLT, dietary restriction and weight loss goals are modest (around 5 % of percent body weight) and a healthy lifestyle is promoted together with attention to the role of nutrition, food and eating in mood regulation. As recommended by Bulik et al. and Sainsbury-Salis [8, 22], internal appetite regulation and self-awareness of hunger and satiety cues are favoured over external regulation of food intake, and approaches are also informed by an understanding of effects of energy restriction [22]. HAPIFED differs from CBT-E in including obesity risk and maintaining factors in the personalised formulation, psychoeducation for obesity, self-monitoring of appetite regulation, weight loss management via behavioural activation and promotion of physical activity with the participation of a multidisciplinary team (psychologist, dietitian, physician and occupational or activity therapist). An important feature of HAPIFED is also the increased number of sessions (30), and the treatment period of 6 months, which is one third more sessions and 2 months longer than usual CBT-E [18].

Table 1 shows the similarities and differences between CBT-E and HAPIFED. To avoid bias from effects of therapy duration in this proposed randomised controlled trial (RCT), the CBT-E broad version will be used, which may be extended to 30 sessions, and has additional modules addressing psychological- maintaining factors, namely clinical perfectionism, core low self-esteem and interpersonal problems [18].

**Table 1 Tab1:** Similarities and differences between the trial therapies

Included	HAPIFED	CBT-E
Personalised ED CBT formulation	Yes, includes obesity	Yes, ED only
Psychoeducation	Yes, ED and obesity	Yes, ED only
Nutritional counselling	Yes, dietician led	Yes, not dietician led
Behavioural monitoring	Yes, with appetite cues	Yes
Multidisciplinary	Yes	No
Session (number)/duration (months)	30/6	30/6
Weight loss management included	Yes	No
Behavioural activation	Yes	No
‘Healthy’ exercise encouraged	Yes	No
Emotion regulation skills	Yes	Yes

*CBT* cognitive behavioural therapy, *CBT-E* cognitive behavioural therapy-enhanced, *ED* eating disorders, *HAPIFED* Healthy Approach to WeIght management and Food in Eating Disorders

The primary aim of this paper is to detail the protocol (version registered as at 11 July 2015) of a single-blind superiority RCT that compares HAPIFED with CBT-E in weight loss efficacy. A second aim will be to investigate the safety of the introduction of weight loss management particularly for people with BN, but also for those with BED who are overweight/obese.

The primary hypothesis of the RCT will be that at end-of-treatment, 6-month and 12-month follow-up, participants receiving HAPIFED will have lost more body weight than those receiving CBT-E. Secondary hypotheses will be that participants receiving HAPIFED compared to CBT-E group will have significantly improved indicators of weight management e.g., reduced body waist measurement, improved cardiovascular and metabolic status, and that participants in either group who achieve binge eating remission will achieve a greater degree of weight loss.

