## Method/Design

### Participants

This study will comprise 100 participants recruited from both community and clinics. Assessments and therapy will be conducted in the Eating Disorders Programme (PROATA) clinic in the Department of Psychiatry of the Federal University of São Paulo (UNIFESP), Brazil. The inclusion criteria are: age ≥ 18 years; either sex; a primary eating disorder diagnosis of BN or BED type according to the *Diagnostic and Statistical Manual of Mental Disorders, fifth edition* (DSM-5) and/or the proposed *International Classification of Diseases, eleventh version* (ICD-11) criteria [2, 3]; and a body mass index (BMI) ≥ 27 and < 40 kg/m^2^. The exclusion criteria are: a current diagnosis of psychosis or bipolar disorder and/or a high level of suicide risk; use of weight loss medication; history of bariatric surgery; clinical conditions that interfere with appetite regulation (e.g., Prader-Willi and Cushing syndromes); and currently receiving psychological treatment for eating disorders.

The present study *a priori* power analysis was based on the estimate of a moderate between group effect size (i.e., 0.6) in the primary outcome of weight loss. To achieve this with power of 0.8 and 1-tailed alpha *p* < 0.05, a minimum of 36 participants per group is required according to Cohen’s tables. Allowing for attrition the sample size is 50 per arm and 10 per therapy group.

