### Data collection, management and analysis

Researchers conducting outcome data entry will be blind to the study group of participants. Between-group outcome analyses will not begin until after the final 1-year follow-up. Governance of data and an independent Data Monitoring Committee (DMC) responsible for interim mid-point in recruitment safety and futility analyses of de-identified data will be conducted at the University of Western Sydney site. The DMC will be composed of a biostatistician with expertise in RCTs, and two senior independent clinical researchers with expertise in RCTs. The trial will be discontinued if assessed to be futile and/or participants’ binge eating is increasing significantly and/or attrition is over 50 %. Therapists under supervision who are not blind to treatment arm will be responsible for the safety of individual participants and will receive directly any concerns about an individual from the DMC.

STATA (StataCorp, College Station, TX, USA) for most statistics will be used. Baseline univariate between-group tests will be done to compare groups on outcome variables, clinical and demographic data. Data will be analysed following ‘intention-to-treat’ principles. Generalised estimating equations [49] with a logit response function will be used for dichotomous outcomes, such as achieving a 5 % reduction in body weight. Linear mixed effects modelling [50] will be used to test for between-group differences in the continuous outcome measures, namely weight loss, levels of ED symptom change, adaptive function, quality of life, depression and anxiety levels, waist circumference, blood pressure, and biochemical markers such as circulating lipid or glucose levels. Putative covariates will be diagnostic group (BN or BED) and use of psychotropic medication. Predictors of outcomes at 6-month and 12-month follow-up to be tested will include the rate of early (by mid-treatment) reduction in binge eating.

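### The aim of establishing safety in bulimia nervosa is not answered by the analysis described: diagnosis is only a covariate, eating-disorder outcomes are tested only for a difference, and the binge-eating stopping rule names neither arm nor diagnosis

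*Protocol article*

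**What the plan says.** The Background describes a "single-blind superiority RCT that compares HAPIFED with CBT-E in weight loss efficacy" and then gives a second aim: to "investigate the safety of the introduction of weight loss management particularly for people with BN". The same sentence extends that aim to people with BED. Earlier, the Background says the safety of weight-loss treatment in BN still needs research. The hypotheses that follow the aims contain none on safety and none specific to BN.

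Under Participants, eligibility requires "a primary eating disorder diagnosis of BN or BED type"; no number or share of BN is given. The sample size there rests on weight loss alone.

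Under Data collection, management and analysis:
- "Putative covariates will be diagnostic group (BN or BED) and use of psychotropic medication".
- Linear mixed models "will be used to test for between-group differences in the continuous outcome measures, namely weight loss, levels of ED symptom change" and further outcomes. No margin or interval-based criterion is stated.
- The trial is to be discontinued if judged futile and/or if participants' "binge eating is increasing significantly and/or attrition is over" one half. The sentence does not mention arm or diagnosis.
- "Therapists under supervision who are not blind to treatment arm will be responsible for the safety of individual participants".

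The Discussion expects the trial to inform the size of future trials on whether HAPIFED can achieve weight loss while matching CBT-E on eating-disorder symptoms.

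**The concern.** The article treats BN as the group in which safety is unknown, because dietary restriction could feed the binge cycle there. Answering that needs an estimate of how HAPIFED compares with CBT-E among people with BN. A main-effect term for diagnosis lets BN and BED differ in average symptom level but still assumes the same treatment effect in both. If HAPIFED did harm only in BN, the common effect would blend it with the BED result, and a test for a difference would probably be non-significant. Such a result is not evidence of safety.

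The stopping rule adds a second weakness. Both therapies contain CBT elements intended to reduce bingeing. If the rule is applied to all participants together, a rise under HAPIFED can be hidden by a fall under CBT-E. At stake is what the trial can say about the group whose safety it sets out to examine.

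**Working it through.** **1. The plan's own figure.** Inputs from Participants: effect size 0.6, power 0.8, one-tailed alpha 0.05. Normal approximation: n = 2(1.645 + 0.842)²/0.6² = 34.3, so 35 per group. The t-test solution is 35.04, so 36. The stated 36 per group reproduces, and 36/(1 − 0.28) = 50 matches 50 per arm with 28% attrition. The sample size is right for weight loss; it was not derived for any eating-disorder or BN-specific question.

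**2. Dilution under a common treatment effect.** Assumptions, not in the document: BN share p, equal in both arms; HAPIFED worsens an eating-disorder outcome by 0.5 SD in BN and has no effect in BED; 50 per arm; two-sided 0.05; no attrition.

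Pooled effect = p × 0.5. Noncentrality = pooled effect × √(50/2). For p = 20%: 0.2 × 0.5 = 0.1 SD; 0.1 × 5 = 0.5; power about 8%.

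| BN share | Pooled effect (SD) | Two-sided power |
|---|---|---|
| 10% | 0.05 | 6% |
| 20% | 0.10 | 8% |
| 30% | 0.15 | 12% |
| 40% | 0.20 | 17% |
| 50% | 0.25 | 24% |

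A larger assumed harm of 0.6 SD in BN gives 6% to 32% over the same shares. If in addition BED improved by 0.3 SD, the pooled effect would be 0.6p − 0.3(1 − p): −0.21 SD at 10% BN and +0.15 SD at 50%. Harm in BN could then appear as no difference or as benefit.

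**3. Precision of a BN-only contrast.** Half-width of the 95% CI in SD units = t(0.975, 2n − 2) × √(2/n), with n BN participants per arm:
- n = 5 (10% BN): 2.306 × 0.632 = 1.46
- n = 10 (20%): 2.101 × 0.447 = 0.94
- n = 15 (30%): 2.048 × 0.365 = 0.75
- n = 25 (50%): 2.011 × 0.283 = 0.57

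These are before attrition. A test of the arm-by-diagnosis term is also weak: for an interaction of 0.6 SD at 50 per arm, power is 15% at a 10% BN share and 32% at 50% (normal approximation, SE = √(2/n_BN + 2/n_BED)). The BN result can therefore only be an estimate.

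**4. Stopping rule read literally.** Illustration with assumed changes: binge eating rises 0.3 SD under HAPIFED and falls 0.8 SD under CBT-E. With equal arms the overall change is (0.3 − 0.8)/2 = −0.25 SD, a fall, although the arms differ by 1.1 SD.

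**The case against.** Much of this could be called detail that an article leaves to an analysis plan or a DMC charter. Neither is shown, and either could add a BN analysis or displays by arm. That limits the point to the analysis as described. It does not remove it, because the article does assign diagnosis a role, does choose a test and does word a stopping rule, and these do not match its stated aim.

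Three stronger readings are tempting, and the document does not support them.
- *The BN question cannot be answered at all.* Table 2 schedules the Eating Disorder Examination at baseline, end of treatment and follow-up, and the self-report eating measures at mid-treatment as well. Diagnosis is recorded, so BN data by arm can be produced.
- *A non-significant result will be reported as safe.* Nothing says so, and the Discussion leaves the comparison with CBT-E on eating-disorder benefit to future trials.
- *The DMC will look only at pooled data.* The rule is silent on arm. De-identified does not mean blind to arm, and a futility assessment would normally need data by arm. Pooling is one reading of an ambiguous sentence.

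Two further points stand. Purging and vomiting occur mainly in BN, so the dilution figures, built for an outcome common to both diagnoses, do not carry over to them directly. And the main limit on BN precision is sample size, which a new model term does not cure. Oversight by therapists and the DMC protects participants but does not estimate an arm difference in BN.

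**Conclusion.** The concern holds as a mismatch between a stated aim and the stated method. Followed as written, the analysis gives no BN-specific comparison of HAPIFED with CBT-E, and for an outcome shared by both diagnoses it would have about 8% power against a 0.5 SD harm confined to a 20% BN subgroup (about 6% to 24% for shares of 10% to 50%). The BN share and the size of harm are assumptions, but power is low across the whole range shown. The stopping-rule part is conditional: offsetting between arms follows only if the rule is applied to all participants together, which the wording permits but does not require. This should be corrected; it does not affect the primary weight comparison.

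**What to change.** - For binge eating, purging and the Eating Disorder Examination global score, add an arm-by-diagnosis term and report the HAPIFED minus CBT-E difference with 95% CI separately in BN and in BED.
- State in advance that the BN result is estimation only, in line with the Discussion, and give the expected precision for plausible BN numbers.
- Rest any safety statement on the confidence interval, not on a non-significant test.
- State that the DMC sees change in binge eating by coded arm, overall and in BN, with the between-arm difference. Any clinical threshold stays with the DMC.

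The cost is wording in the analysis and DMC sections; no new data are needed. The downside is wide BN intervals and a softer safety claim.

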## Method/Design

### Participants

This study will comprise 100 participants recruited from both community and clinics. Assessments and therapy will be conducted in the Eating Disorders Programme (PROATA) clinic in the Department of Psychiatry of the Federal University of São Paulo (UNIFESP), Brazil. The inclusion criteria are: age ≥ 18 years; either sex; a primary eating disorder diagnosis of BN or BED type according to the *Diagnostic and Statistical Manual of Mental Disorders, fifth edition* (DSM-5) and/or the proposed *International Classification of Diseases, eleventh version* (ICD-11) criteria [2, 3]; and a body mass index (BMI) ≥ 27 and < 40 kg/m^2^. The exclusion criteria are: a current diagnosis of psychosis or bipolar disorder and/or a high level of suicide risk; use of weight loss medication; history of bariatric surgery; clinical conditions that interfere with appetite regulation (e.g., Prader-Willi and Cushing syndromes); and currently receiving psychological treatment for eating disorders.

The present study *a priori* power analysis was based on the estimate of a moderate between group effect size (i.e., 0.6) in the primary outcome of weight loss. To achieve this with power of 0.8 and 1-tailed alpha *p* < 0.05, a minimum of 36 participants per group is required according to Cohen’s tables. Allowing for attrition the sample size is 50 per arm and 10 per therapy group.

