Single blinding will be achieved by not informing participants of any specific details of the therapy content. The information at recruitment that will be provided to participants regarding the therapy is as follows: ‘We have developed an approach that integrates techniques from cognitive behavioural therapy for eating disorders with behavioural strategies for weight loss. One is called HAPIFED (a Healthy Approach to Weight Management and Food in Eating Disorders), and the other is called cognitive behavioural therapy-enhanced … If you agree to participate in this study and have met all the inclusion criteria and if outpatient therapy is suitable for you, you will be randomly allocated (through an online programme) to a group therapy programme that will comprise twice-weekly group over about 1 month … You will have an equal chance (like tossing a coin) of participation in one or other treatment’ (translated from Brazilian Portuguese by author PH). Participants will not be informed if they will be in a HAPIFED or in a CBT-E therapy group at any point, and any treatment materials provided to participant will not be identified as being from either HAPIFED or CBT-E manuals.

Those who will be considered eligible for the study will be randomised in blocks of 20 (2 therapy groups) using an online site (www.sealedenvelope.com). One hundred participants will be allocated over 18 months to 10 groups with 10 participants in each group. Five groups will receive HAPIFED (experimental group) and five will receive CBT-E (control group). An investigator external to the site (PH) will administer the allocation which will be concealed and revealed only to trial therapists and therapy supervisors until the final participant completes follow-up.

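### The power statement treats participants as independent although both therapies are delivered in ten fixed groups of 10; power should be restated with an assumed intra-group correlation, and therapy group named in the models

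*Protocol article*

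**What the plan says.** Under Participants, the power analysis assumes a "moderate between group effect size (i.e., 0.6) in the primary outcome of weight loss", with "power of 0.8 and 1-tailed alpha *p* < 0.05". On that basis "a minimum of 36 participants per group is required according to" published tables. The next sentence reads "Allowing for attrition the sample size is 50 per arm and 10 per therapy group". No ICC, design effect or number of therapy groups enters the calculation.

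The abstract says that participants "will be recruited from both community and clinics and individually randomised to a therapy arm". The Procedure section then has "One hundred participants will be allocated over 18 months to 10 groups with 10 participants in each group", five groups for each therapy. In both arms one session is individual and the other 29 are group sessions over six months.

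Under Data collection, management and analysis, "Linear mixed effects modelling [50] will be used to test for between-group differences in the continuous outcome measures", and generalised estimating equations (GEE) are planned for dichotomous outcomes. Diagnosis and psychotropic medication are the putative covariates. The section states neither the random effects of the mixed models nor the clustering unit of the GEE.

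Under Treatment fidelity, therapists deliver both treatments, in order to control therapist effects. Nothing comparable is said about therapy groups.

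**The concern.** Individual randomisation makes the participants independent at entry but does not keep them so. Members of a therapy group share leaders, peers and 29 sessions, and the article says that BMI is also monitored weekly in session. Weight change may therefore be more alike within a group than between groups. Each group lies wholly within one arm, so any group effect adds to the variance of the HAPIFED minus CBT-E difference. Having the same therapists deliver both treatments does not remove it.

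Two things are at stake, and they are largely alternatives. If the analysis allows for therapy group, the error rate is protected but power is lower than stated. If it does not, most of the apparent power remains, but the standard error is too small and the test rejects too often under the null.

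**Working it through.** **Inputs.** From the article: d = 0.6 in SD units, one-sided alpha 0.05, power 0.8, 36 evaluable and 50 recruited per arm, five groups of 10 per arm. The attrition implied is 1 - 36/50 = 28%, which leaves 36/5 = 7.2 evaluable per group. The ICC is not given; the range 0.01 to 0.10 is my assumption.

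**Step 1: reproduce the stated figure.** A two-sample t-test with independent observations needs n = 35.04 per arm, hence 36, with power 0.809 at 36. The two-sided version needs 45. So 36 is the one-sided figure for independent observations, and 36/(1 - 0.28) = 50 uses the whole increase for attrition.

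**Step 2: add the groups.** Design effect DE = 1 + (m - 1) × ICC, effective n = n/DE, non-centrality = 0.6 × √(effective n / 2). Five groups per arm leave 2 × (5 - 1) = 8 between-group df. Example at 36 per arm and ICC 0.05: DE = 1 + 6.2 × 0.05 = 1.31; effective n = 36/1.31 = 27.5; non-centrality = 0.6 × √13.74 = 2.22. Normal power = Φ(2.22 - 1.645) = 0.72. From the non-central t on 8 df (critical value 1.860) it is 0.65.

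| n per arm (per group) | ICC | DE | Power, normal | Power, 8 df |
|---|---|---|---|---|
| 36 (7.2) | 0 | 1.00 | 0.816 | 0.751 |
| 36 (7.2) | 0.01 | 1.06 | 0.795 | 0.729 |
| 36 (7.2) | 0.05 | 1.31 | 0.719 | 0.650 |
| 36 (7.2) | 0.10 | 1.62 | 0.639 | 0.573 |
| 50 (10) | 0 | 1.00 | 0.912 | 0.862 |
| 50 (10) | 0.01 | 1.09 | 0.890 | 0.835 |
| 50 (10) | 0.02 | 1.18 | 0.868 | 0.809 |
| 50 (10) | 0.05 | 1.45 | 0.801 | 0.735 |
| 50 (10) | 0.10 | 1.90 | 0.702 | 0.634 |

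The row at 36 per arm and ICC 0 separates the two sources of loss: the move to 8 df alone takes power to 0.751, and the correlation accounts for the rest.

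**Step 3: where 0.8 is lost.** At 36 per arm, power falls below 0.8 from an ICC of about 0.008 (normal) and at any ICC on 8 df. At 50 per arm it holds up to an ICC of about 0.05 (normal) or 0.02 (8 df).

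**Step 4: if therapy group were left out.** The expected pooled variance is 1 - ICC × (m - 1)/(n - 1), and the true one-sided error is 1 - Φ(1.645 × √(pooled variance / DE)). At ICC 0.10 with 50 per arm: pooled variance = 1 - 0.10 × 9/49 = 0.982; √(0.982/1.90) = 0.719; error = 1 - Φ(1.183) = 0.119. The range from 36 to 50 per arm is 0.055-0.058 at ICC 0.01, 0.076-0.087 at 0.05 and 0.100-0.119 at 0.10. Simulation with 40,000 trials at 7 and 10 per group agrees (0.055-0.057, 0.075-0.086, 0.102-0.118).

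These figures take group effects as independent between groups. The arms run in pairs, in blocks of 20. If half of an ICC of 0.10 were shared by the two groups of a block, the simulated error at 10 per group would be about 0.085; if all of it were shared, about 0.044.

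**Step 5: cost of a cohort term.** Ten groups less one mean, one arm and four cohort terms leave 4 df. If cohort explains no variance, power at 36 per arm is then 0.65, 0.58 and 0.50 at ICC 0.01, 0.05 and 0.10, and at 50 per arm 0.76, 0.66 and 0.56.

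**The case against.** A reader might infer that the type I error of the primary test is inflated. The document does not support that. It plans mixed models and GEE without giving their levels. The listed items are putative covariates, and a random effect is not a covariate. A condensed article may leave this structure to an analysis plan that is not shown here. Inflation needs both an ICC above zero and a final model without therapy group, and it shrinks when the correlation is shared between the arms within a cohort.

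A reader might also infer that power of 0.8 cannot be reached. That too goes too far. The Assessment section has everyone assessed, including those who stop treatment, and the analysis follows intention-to-treat, so 36 per arm is the planning minimum and not necessarily the number analysed. At full retention a small ICC is absorbed. Part of the loss comes from the 8 df and not from the correlation, and the ICC itself is assumed.

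All of this stands, and it limits the claim. It does not rescue the power statement: the 36 assumes independence, and the 14 additional participants per arm were assigned to attrition and cannot be counted again for clustering.

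**Conclusion.** The concern holds for the power statement. The claim of power 0.8 at 36 per arm takes no account of delivery in groups. With therapy group in the model and 8 df, power at that minimum is about 0.73, 0.65 and 0.57 for ICC 0.01, 0.05 and 0.10 (normal approximation 0.80, 0.72 and 0.64). At 50 per arm, 0.8 is kept only for an ICC up to about 0.02 on 8 df, or 0.05 by the normal approximation.

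The error-rate side is conditional: about 5.5-6% at ICC 0.01, and up to about 10-12% at ICC 0.10, if therapy group is omitted and the arms share none of the correlation. All these sizes rest on the assumed ICC range, equal group sizes and a single comparison of two means, which is also the setting of the plan's own calculation.

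**What to change.** - Under Data collection, management and analysis, name therapy group as a random effect in the linear mixed models and as the cluster in the GEE. Add a small-sample correction: for example Kenward-Roger for the mixed models, and a bias-corrected variance for the GEE, since there are only ten clusters.
- Under Participants, restate the power over a stated ICC range with five groups per arm, at 36 and at 50 per arm.
- Report the observed ICC with the results.
- Treat a fixed effect for cohort (the block of 20) as optional. It could remove variance shared by the two arms, but it cuts the between-group df from 8 to 4; if it is used, restate the power on 4 df.

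The cost is wording, wider confidence intervals and a less favourable power figure. No extra patients are needed, and the Procedure already assigns every participant to a therapy group. Recruitment has started, but between-group outcome analyses are not to begin until after the final one-year follow-up, so the change can still be specified in advance.
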